**Fig. 1 Fig1:**
[figure not shown]
PISTACHIo study workflow

### Smartwatch technology and momentary assessments

This study will use Garmin vivosmart4 smartwatches (previously used in IRB application 20–002,133 preliminary study) to monitor the step count, sleep quality, heart rate (resting and active), and activity rates (i.e., how often subject moves). These data are available with granularity of each minute and will be recorded through Fitabase for both parents and children. Furthermore, for those in the active PCIT-AI arm, the child’s watch will feed data into mEMA that will trigger a behavioral alert to be sent to the parent participant. Study staff will walk the parents/guardians through how to download the Garmin Connect and mEMA applications on their smartphones or tablets to allow for syncing of the data from the smartwatch to Fitabase or mEMA. Families who do not have their own smartphone or tablet will be provided with an iPod. We note that the choice of iPod for the study was made prior to Apple Inc.’s announcement of discontinuing the product’s manufacturing (May 10, 2022), but the iOS 16 will support the iPods until the study’s anticipated end date. Families will be guided to synchronize data at a minimum once at each PCIT appointment, yet ideally, every night. Garmin watches are waterproof, and participants will be encouraged to wear them at all times during the 12 weeks of treatment (minimum of 70% of the time, 70% of the days). The choice of 70% as a minimum threshold for compliance during the study allows for meaningful imputation of missing values [21]. Acoustic analysis of child vocalizations recorded during sessions will be analyzed using frequency and joint time–frequency modulation methods [22].

### Biological specimen collection for CRP and multi-omics studies

This study will collect 11 mL of blood from both participating subjects (child, parent/significant caregiver) for biomarker discovery efforts. Particularly, this study will use blood to derive C-reactive protein (CRP) levels, genome-wide genomics, proteomics (using Olink® Explore 3072 platform), metabolomics, and exposomics.

CRP is a known marker of chronic inflammation. At high levels, it alerts to acute infection; however, minor elevations can point to stress-related immune dysregulation and has been associated with psychosocial stress [23]. Much is known about effects of elevated CRP levels in adulthood on long-term medical and psychiatric issues (chronic stress); however, little is known about the origins of CRP elevation early in life [24]. To date, there has been only one study that explored CRP in preschoolers that showed no significant correlations between mother’s chronic inflammation and child inflammation [25]. They hypothesized that it might be difficult to detect chronic inflammation in children as young as 3 years old; however, this was only a pilot study. Other studies were able to show strong associations between CRP levels and early childhood stress in children as young as 10 that persisted into adulthood [26].

The exposome is a combination of cumulative environmental influences and associated biological responses throughout the life span, including exposures from the environment, diet, behavior, and endogenous processes [27]. Our prior work with multi-omics has facilitated the discovery of novel biomarkers for studying pathophysiology of disease and/or drug response and the prediction of antidepressant treatment outcomes. Given that the parent–child dyad is characterized by a combination of these factors in addition to inherited factors (i.e., genomics), we hypothesize that integrative analytics of these measures will help identify biomarkers associated with externalizing behavioral outcomes in children. High-resolution mass spectrometry (HRMS) assays will be used to measure the metabolome and exposome.

HRMS analyses follow established protocols using dual liquid chromatography-ultrahigh-resolution mass spectrometry (LC–MS) for metabolomics and gas chromatography-ultrahigh-resolution mass spectrometry (GC–MS) for exposomics with data extraction supporting both targeted and untargeted analyses [28, 29]. Capabilities can identify a very broad spectrum of endogenous metabolites, food and microbiome metabolites, and environmental chemical exposures [28, 29]. The complementary methods detect environmental chemicals, such as PAHs (polycyclic aromatic hydrocarbons), organochlorine pesticides, PCBs (polychlorinated biphenyls), PBBs (phosphate-buffered saline), PBDEs (polybrominated diphenyl ethers) with GC methods, and more polar metabolic products and water-soluble pollutants such as PFAS (per- and polyfluoroalkyl substances) with LC methods [28–30].

Bioinformatic and biostatistical methods are well-developed to detect discriminatory features, metabolites, and environmental chemicals and determine unique exposure patterns such as relative quantities, chemical correlations, and interactive effects of environmental chemicals and metabolic pathway enrichment [31–33]. Approaches using machine learning, mixture modeling, and network analysis tools, such as xMWAS [31, 32], provide powerful approaches for omics data integration, network analysis, and visualization of specific exposome associations to EBP [31–33]. Such exposome and metabolome-wide association studies in these parent–child dyads will link critical exposures and associated metabolic responses to behavioral outcomes. The multi-omics framework will deepen understanding of complex molecular interactions, metabolic perturbations, potential novel biomarkers, and causal mechanisms related to externalizing behavior outcomes.

### Data confidentiality

All nonelectronic questionnaires administered throughout the study will be stored in locked drawers in a secure office. Deidentified data will be entered into a REDCap database that will be protected with passwords available to limited study personnel. Deidentified electronic data from the Garmin smartwatch and mEMA applications will be uploaded on Fitabase and Ilumivu’s password-protected secure websites respectively. Both Fitabase (product of Small Steps LLC) and mEMA (product of Ilumivu) are HIPAA compliant in that no PHI data is needed for data collection and aggregation. Only authorized users will have access to these websites through unique identifiers and passwords. The electronic data will be downloaded to a file available to limited study personnel, and that could only be accessed through Mayo Clinic’s secure intranet on a local computer of the study team.

### Proposed analysis

This study is an exploratory clinical trial with the broad goals of demonstrating feasibility, producing pilot data, generating validate effect sizes, and informing future larger, multicenter trials. The level of significance will be set at *α* = 0.05 (two tailed), and to address multiple testing (where applicable), *p*-values will be adjusted using the false discovery rate. We estimated the sample size for this pilot study based on the hypothesis examining clinical outcome (ECBI) between the PCIT-AI group and PCIT-sham group (hypothesis 2a). We anticipate that a sample size of 50 participants per group (*N* = 100) achieves 70% power, at a 0.05 alpha level (two tailed) to detect an odds ratio of 2.0 favoring PCIT-AI with the proposed randomized design. To evaluate feasibility of the use of Garmin wearables, we will use descriptive statistics assessing the frequency of Garmin use in participants (70% or greater is defined as success for this hypothesis). A linear mixed model analysis of repeated measures will be used to evaluate the interaction effects of type of PCIT (AI informed or AI sham), time, and ECBI scores. A separate linear mixed model analysis will be used to evaluate the interaction effects of PCIT type (AI informed or AI sham), time, and PSQ scores with ECBI scores as a covariate. To evaluate concordance of sleep cycle data from children aged 3–7 as compared to parental rating scales of PSQ, we will use Spearman correlation coefficients and mixed linear regression models. Separate Spearman correlations and a mixed linear regression model will examine the relationship between biometric data from smartwatches (heart rate and movement) with weekly ECBI reports. Partial least-square regression networks will be used to derive multi-omic integration networks, and Spearman correlation will then be used to associate omics with physiological measures from smartwatches.

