**Methods:**

This randomized double-blind controlled study aims to recruit a total of 100 participants, consisting of 50 children aged 3–7 years with an EBP measure rated above the clinically significant range (T-score ≥ 60) (Eyberg Child Behavior Inventory-ECBI; Eyberg & Pincus, 1999) and their parents who are at least 18 years old. Participants are randomly assigned to the artificial intelligence-PCIT group (AI-PCIT) or the PCIT-sham biometric group. Outcome parameters include weekly ECBI and Pediatric Sleep Questionnaire (PSQ) as well as Child Behavior Checklist (CBCL) obtained weeks 1, 6, and 12 of the study. Two smartphone applications (Garmin connect and mEMA) and a wearable Garmin smartwatch are used collect the data to monitor step count, sleep, heart rate, and activity intensity. In the AI-PCIT group, the mEMA application will allow for the ecological momentary assessment (EMA) and will send behavioral alerts to the parent.

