## Methods

Our clinical trial is examining the AI-PCIT for treatment of externalizing behavioral problems in young children. Participants are recruited from Young Child Behavioral Clinic (YCBC) at Mayo Clinic in Rochester, MN, USA, and through advertisements at local pediatrics and family medicine clinics. Interested participants are initially provided information about the study and are scheduled for a consult in the Young Child Behavioral Clinic. The overall recruitment goal for the trial is *N* = 50 participants between ages of 3–7 years whose measure of EBP rated above the clinically significant range (T-score ≥ 60) (Eyberg Child Behavior Inventory-ECBI; Eyberg & Pincus, 1999) [3]. Participants are randomly assigned to AI-PCIT group or PCIT-sham biometric group. Each child is recruited with their parents who are at least 18 years old for a total recruitment of 100 participants. Participants are children aged 3–7 years old. They are of any gender, race, or ethnicity recruited from outpatient or inpatient care. Inclusion criteria include the patients’ ability to provide developmentally appropriate informed assent and legal guardians that are able to provide informed consent. Furthermore, the patient’s EBP severity must be rated above the clinically significant range (≥ 120; T-score ≥ 60) (Eyberg Child Behavior Inventory-ECBI; Eyberg & Pincus, 1999) [3]. The need for more intensive behavioral treatments such as an ER visit or hospitalization for behavioral dyscontrol will not be exclusionary or exit criteria. Participants must be fluent in the English language, have verbal abilities, and have the competency to consent based on ability to provide a spontaneous narrative description of the key elements of the study. Participants also require at least one smartphone and Internet access. Exclusion criteria for the PISTACHIo clinical trial include individuals who are unable to speak and understand English; patients who refuse or withdraw their consent, or those who are unable or unwilling to adhere to study procedures; and patients who do not have a smartphone and access to Internet connection. The study has the approval of the local institutional review board for human subject research protection (Mayo Clinic, Rochester, MN, USA).

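### The 70% power for the ECBI comparison assumes 50 units per group, but the trial recruits 50 children in total, about 25 per arm

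*Protocol article*

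**What the plan says.** The Proposed analysis section says the sample size is "based on the hypothesis examining clinical outcome (ECBI) between the PCIT-AI group and PCIT-sham group", labelled hypothesis 2a. It continues: "We anticipate that a sample size of 50 participants per group", with N = 100 in brackets, "achieves 70% power", "at a 0.05 alpha level (two tailed) to detect an odds ratio of 2.0 favoring PCIT-AI". No control rate, ECBI category split, SD or within-child correlation is given. The analysis named for ECBI is a linear mixed model for repeated measures.

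The recruitment target is stated in two other places. The abstract (Methods) says the study "aims to recruit a total of 100 participants, consisting of 50 children" and their parents. The Methods section sets the goal at N = 50 participants aged 3 to 7 and then explains the larger figure: "Each child is recruited with their parents who are at least 18 years old for a total recruitment of 100 participants".

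The Objectives section describes ECBI as a parental rating scale, completed weekly. Under Study procedures, the parent receives targeted or random messages according to the arm, so a child and parent share one allocation.

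**The concern.** The same total, 100, is a count of people in the abstract and Methods section, and a count of units in a two-group comparison in the power statement. A parent adds no second ECBI outcome: the parent supplies the rating, and the child is the one rated. Fifty children over two arms give half the number per group that the power claim uses.

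This is the only sample-size justification in the article. The abstract's Discussion makes superiority of AI-PCIT over standard PCIT one of the study's goals, and the Conclusion says the study can determine it. A null ECBI result would then be read as coming from a comparison with 70% power, which the recruited number does not give.

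**Working it through.** **Inputs.** Two-sided alpha 0.05, power 70%, odds ratio 2.0 and 50 per group (Proposed analysis); 50 children in total (abstract and Methods); two arms. Allocation 1:1 is assumed, as the equal groups in the power statement imply.

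**Step 1: units per arm.** 100 people = 50 children + 50 parents. One ECBI outcome per dyad gives 50 units, and 50 / 2 = 25 per arm.

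**Step 2: effect of the unit count alone, taking the stated 70% at face value.**
- Noncentrality at 50 per arm: 1.960 + 0.524 = 2.484.
- Halving n multiplies the standard error by √2 = 1.41, so at 25 per arm the noncentrality is 2.484 / 1.414 = 1.757.
- Power = Φ(1.757 − 1.960) = Φ(−0.203) = 0.42 (0.41 with the t distribution).
- No control rate or SD is needed.

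**Step 3: the same in detectable differences** (single continuous comparison, t-test, 70% power): 0.502 SD at 50 per arm and 0.717 SD at 25 per arm.

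**Step 4: does 70% follow from an odds ratio of 2.0 at 50 per arm?** The ECBI outcome behind the odds ratio is not defined, so each line below is an assumption.
- Single binary endpoint, two-proportion test. Power = Φ[(|p2 − p1| − 1.96·SE0) / SE1], where SE0 is the pooled and SE1 the unpooled standard error. Power peaks at a control rate of 0.41. There p2 = (2 × 0.41/0.59) / (1 + 2 × 0.41/0.59) = 0.582, a difference of 0.172.
  - 50 per arm: SE0 = 0.1000, SE1 = 0.0985, power 40.2%.
  - 25 per arm: SE0 = 0.1414, SE1 = 0.1393, power 22.4%.
- Ordinal endpoint with many categories, proportional odds. Power = Φ[√(N·(ln 2)²/12) − 1.96]: 51.6% at N = 100 and 29.3% at N = 50.
- Logistic conversion to a mean difference, d = ln 2 × √3/π = 0.382: 48.0% at 50 per arm and 27.1% at 25.
- One-sided testing at 50 per arm reaches at most 52.9%, 63.9% and 60.5% respectively.

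No single-endpoint version reaches 70% at 50 per arm. For a binary endpoint, 70% at an odds ratio of 2.0 needs at least 105 children per arm.

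**Step 5: precision at 25 per arm.** The 95% CI half-width for a mean difference is 2.011 × √(2/25) = 0.57 SD (t, 48 degrees of freedom).

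**Step 6: attrition, as sensitivity only.** With 25% loss, 25 × 0.75 = 18.75 per arm remain, and power on the face-value effect is about 33%. With 69% loss, 7.75 remain and it is about 16%.

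**The case against.** The strongest objection is that the planned analysis is a repeated-measures mixed model on weekly scores, which can have more power than any single-endpoint calculation. That stands. Suppose, purely as an assumption, that 12 weekly scores are averaged, d is 0.382 and the within-child correlation is 0.3 to 0.7. Power is then about 60% to 89% at 50 per arm and 34% to 60% at 25. At a correlation of 0.5 it is about 73% and 44%. So 70% might be reachable at 50 per arm under some such model, but the article states no correlation or SD, and an odds ratio is not the effect measure of a linear mixed model. In every version 25 per arm gives less power than 50.

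Four stronger readings are tempting but not supported:
- A reader might take 22% as a ceiling on power. It holds only for one binary endpoint with a two-proportion test; the ordinal and repeated-measures figures are higher.
- A reader might attribute the whole fall from 70% to 22% to counting parents. The unit count accounts for 70% to about 42%. Under the binary model, power is already only 40% at 50 per arm, which is a separate fault in the stated figure.
- A reader might apply the 25 to 69% attrition in the Discussion as a forecast. It is a literature range, and the article describes reimbursement and toys to support adherence. Study procedures rules out replacement for participants withdrawn for non-adherence or for meeting exclusion criteria, not explicitly for every dropout.
- A reader might conclude that the authors knowingly entered parents as units. The power statement does not say so; it may have assumed 50 children per group. In that case the recruitment target is half of what the calculation needs, and the passages still conflict.

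It is also fair that this is a pilot whose main aim is feasibility. The 70% wear criterion does not depend on this power. But the article chose to make a formal power claim on ECBI, and that claim has to match the design. A full protocol or SAP could supply missing detail, but would not remove a contradiction within the article.

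**Conclusion.** The power statement is wrong as written. The article recruits 50 children and claims power for 50 per group on a child-level outcome, and nothing in it reconciles the two. With 1:1 allocation the comparison has about 25 units per arm. Accepting the stated 70% at 50 per arm, power is about 42%; this is the measure of the unit error. The 70% is also not reproduced from an odds ratio of 2.0 in any single-endpoint calculation at 50 per arm, and the article gives no inputs from which a repeated-measures figure could be checked. The feasibility objective is unaffected.

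**What to change.** Reconcile the abstract, the Methods section and the Proposed analysis section. In the sample-size paragraph:
- State 50 parent-child dyads, about 25 per arm, with the allocation ratio, and name the child (dyad) as the unit of randomisation and analysis.
- Replace the 70% with the power, or the minimum detectable ECBI difference, at 25 per arm under the planned mixed model, giving the assumed SD and within-child correlation. If the odds ratio is kept, define the ECBI outcome it refers to.
- Add a sensitivity figure for attrition, labelling the cited 25 to 69% as a literature range.
- Present the ECBI comparison as estimation with a 95% CI, noting the expected half-width of about 0.57 SD for a single comparison at 25 per arm.

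The cost is one rewritten paragraph and a less favourable stated power. Enrolment need not change.

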### The need for wearables in promoting parenting practices

PCIT (parent–child interaction therapy) is one of the four behavior parent training (BPT) programs that are considered “well supported by research evidence” by the California Evidence-Based Clearinghouse for Child Welfare [11]. It is a dyadic parent–child therapy technique that is unique due to its utilization of in vivo parent coaching via bug-in-the-ear treatment from a therapist behind one-way glass. Most importantly, PCIT allows for individually tailored coaching that can address personal difficulties of parent–child dyads. A recent meta-analysis of the effectiveness of PCIT, focused mainly on modifications, study design, and bias, showed that PCIT was superior not only in comparing case/control groups for reducing externalizing behaviors but also in helping with parent- and child-related stress [12]. The review additionally showed that PCIT effectiveness was not affected by session length, various settings (academic versus community), or presenting problems (disruptive behaviors alone as compared to other problems complicated by disruptive behaviors). Moreover, PCIT’s unique focus on goal criteria makes the components of PCIT ideal for modifications [12].

Despite PCIT effectiveness, high dropout rates (in some studies as high as 50%) prior to completion of the treatment remain a significant problem [13]. Currently, there are some efforts to reduce high attrition by the use of new technologies such as telehealth which remotely delivers real-time therapy to the patient’s home [14]. Another significant challenge lies in the ability to frequently engage and remind parents of the parenting practices taught during PCIT sessions [15]. The current study aims to examine and facilitate further development of an innovative artificial intelligence PCIT (AI-PCIT) protocol augmented with wearable technologies such as smartwatches.

Wearable technologies such as smartwatches allow for objectively measuring activities that extend beyond observations reported in the clinical settings. Wearables have been tested for continuous monitoring during pregnancy [16] and promoting physical activity in adolescents with juvenile idiopathic arthritis [17]. Despite the clinical need, wearable technologies have not been widely studied nor implemented for the treatment of young children with EBP.

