### Study procedures

The PISTACHIo clinical trial utilizes a randomized, double blind, design to compare the active PCIT-AI group and PCIT-sham (treatment as usual) group. The child and primary caretaker are fitted with Garmin watches that are required to be worn for a minimum of 70% of the days during their 12 weeks of treatment. In addition to this, we require the participants to wear the watch for at least 70% of every 24 h per the principal investigator’s discretion. Families are scheduled for PCIT treatment with PCIT-certified therapist in the Young Child Behavioral Clinic. Before the first PCIT treatment session, all participants are randomized into an active versus sham arm of the study. This is done by using a computer-generated list based on a stratified randomization scheme and using a permuted block method with a random number generator. The research assistant, research coordinator, and computer engineer who monitors Garmin apps are the only team members aware of which group the participant belongs to (active vs sham) [20]. Study investigators, clinical/cognitive raters, and participants are blind to the treatment condition. Parents in the AI-PCIT group are receiving targeted messages that instruct them on how to de-escalate their child when the Garmin device recognizes vital signs associated with a child’s tantrum. Parents in the PCIT-sham group receive random messages throughout the day with various relaxation strategies such as reminders to practice deep breathing with their child. The treatment is overseen by board-certified child and adolescent psychiatrist who is a Within-Agency PCIT Trainer.

Any participants withdrawn from the study if they were non-adherent to study procedures or met exclusion criteria at any point after the consent will not be replaced, and their data will not be used for analysis. Additionally, broken watches will be replaced, and therefore, the participant will not be excluded from the study.

The ongoing clinical trial study protocol conforms to the International Consolidated Standards of Reporting Trials (CONSORT) guidelines and is registered on Oct 14, 2021, in clinicaltrials.gov (ID: NCT05077722), an international clinical trial registry. See Fig. 1 depicting the PISTACHIo study workflow and timing for study procedures.

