## Discussion

Currently, there are no AI-augmented treatments for young children with EBP. PCIT is an evidence-based behavioral treatment for 3–7 years old with EBP supported by numerous meta-analyses studies [12, 34, 35]. Attrition rates in PCIT are high and can reach 25 to 69% depending on the study [13, 36]. Factors such as education, income, family employment, and parents’ engagement have been cited as main reasons for attrition [37].

Our study is first to offer AI-augmented PCIT treatment for young children with EBP which will allow for improved engagement of families. The main goal of PCIT is to strengthen the relationship between the parent and child. With the use of our Garmin technology, we can augment that goal by sending targeted messages to parents in critical moments when their child needs help. What is particularly innovative about our project is that the chosen smartwatch does not require the young child to spend time in front of a screen or to interact with an app, both situations that many parents are opposed to for children of this age range. Instead, it helps parents to remember important therapy techniques during real-world parent/child interactions which can be vital learning opportunities for the dyad.

Our study additionally provides us with a valuable environment to test the relationship between multi-omic associations of disruptive behaviors in a parent–child dyad and associations with physiological smartwatch measures. This has never been studied in children with EBP.

It is important to note that data privacy is a significant concern in mobile health, particularly in the research area. As a procedure at enrollment, the study team disengages location, calendar, contacts, social media, and microphone settings on the Garmin Connect and mEMA applications. However, the study will not stop participants from using their discretion to change these settings should they choose to utilize additional features commodity smartwatches provide. Additionally, all self-reported assessments through the mEMA application are deidentified as the connection between the application, and the Ilumivu website is done through a randomly generated code accessed by IRB-approved study personnel.

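### The 70% power is quoted at the full recruitment number, with no allowance for participants whose data the plan discards

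*Protocol article*

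**What the plan says.** Proposed analysis sizes the study "based on the hypothesis examining clinical outcome (ECBI) between the PCIT-AI group and PCIT-sham group (hypothesis 2a"). It continues: "We anticipate that a sample size of 50 participants per group", written there as N = 100, "achieves 70% power, at a 0.05 alpha level (two tailed) to detect an odds ratio of 2.0 favoring PCIT-AI". It mentions no attrition.

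The Abstract and Methods both put total recruitment at 100 people, made up of 50 children and their parents.

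On loss, the section on the need for wearables says that "high dropout rates (in some studies as high as 50%) prior to completion of the treatment remain a significant problem". The Discussion says: "Attrition rates in PCIT are high and can reach 25 to 69% depending on the study". Study procedures says that participants withdrawn for non-adherence, or because they met an exclusion criterion after consent, "will not be replaced, and their data will not be used for analysis". The exclusion criteria in Methods include "patients who refuse or withdraw their consent, or those who are unable or unwilling to adhere to study procedures".

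**The concern.** The number that carries the power equals the number to be recruited. For the 70% to apply, every recruited participant would have to reach the analysis. The plan's own handling rule works against that: certain withdrawn participants leave the analysis set and nobody takes their place. Withdrawal of consent and failure to adhere both fall under the rule through the exclusion criteria. For these participants the linear mixed model cannot make use of partial weekly ECBI data, because the data are set aside before analysis.

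The between-arm ECBI comparison is the only hypothesis the sample size rests on. The Abstract lists finding out whether AI-PCIT is superior among the study's goals, and the Conclusion says the study is placed to settle that question. A reader who trusts the 70% could take a null ECBI result as evidence of no benefit when the comparison had much less power than stated.

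**Working it through.** **Inputs.** From Proposed analysis: two-sided alpha 0.05, power 70%, odds ratio 2.0, 50 per group. From the Abstract and Methods: 50 children, which is 25 per arm at 1:1. From the Discussion: 25% and 69% attrition. From the section on the need for wearables: 50%. No control rate, response definition, SD or correlation is given.

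**1. The plan's own figure.** For a binary outcome, p2 = 2·p1/(1 − p1 + 2·p1). Since no control rate is stated, I scanned p1 from 0.01 to 0.985. The most favourable value is about 0.415, which gives p2 = 0.83/1.415 = 0.587. With the pooled variance under the null, SE0 = 0.1000 and SE1 = 0.0985, so power = Φ[(0.1716 − 1.960 × 0.1000)/0.0985] = Φ(−0.248) = 40.2%. Two other two-sided readings at 50 per group are:
- Ordinal proportional odds: Φ(√(50/6) × 0.693 − 1.960) = 51.6%.
- Odds ratio converted to a standardised difference, d = 0.693 × √3/π = 0.382: Φ(0.382 × √25 − 1.960) = 48.0%.

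Neither reaches 70%, and one-sided versions of all three stay at or below 63.9%. A binary outcome needs at least 105 per group for 70%. A gain from repeated measures could close the gap, but no correlation is stated from which to compute it. The 70% therefore does not reproduce. It is granted below only to isolate the effect of loss.

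**2. Margin for loss.** Number in the power statement: 100. Number recruited: 100. Margin: 0.

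**3. Effect of loss, granting 70% at 50 per group.** The implied noncentrality is 1.960 + 0.524 = 2.484. With a fraction a lost equally in both arms and all their data discarded, power = Φ(2.484·√(1 − a) − 1.960).

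| Loss | Analysed per group | Power |
|---|---|---|
| 0% | 50 | 70% |
| 25% | 37.5 | Φ(0.192) = 57.6% |
| 50% | 25 | Φ(−0.203) = 41.9% |
| 69% | 15.5 | Φ(−0.577) = 28.2% |

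**4. Same basis, counted in children.** The ECBI is scored per child and 25 children per arm are recruited, so the noncentrality is further multiplied by √(25/50): power = Φ(2.484·√(0.5·(1 − a)) − 1.960).

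| Loss | Analysed children per arm | Power |
|---|---|---|
| 0% | 25 | 41.9% |
| 25% | 18.75 | 33.0% |
| 50% | 12.5 | 23.6% |
| 69% | 7.75 | 16.3% |

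The tables must not be mixed. For example, 58% belongs to 37.5 per group, not to about 19 children per arm.

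**The case against.** Four points can fairly be made for the plan.

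- **The attrition figures come from other PCIT studies**, in wording that gives ranges or upper ends. The Discussion expects better family engagement here, and the article describes reminders, weekly reimbursement and toys for wearing the watch. A reader might infer that the protocol predicts 25 to 69% loss for this trial. It does not. The figures serve only to illustrate a range.
- **Not every dropout is discarded.** The rule covers participants withdrawn for non-adherence or for meeting an exclusion criterion. A family that misses late sessions without being withdrawn could keep its weekly ECBI scores in the mixed model. A reader might infer that all cited attrition turns into lost data. That is a worst case the text does not establish.
- **The sentence is conditional, and the article is condensed.** A stated N giving a stated power is not a miscalculation merely because loss is left out, and a fuller protocol may hold an attrition assumption. But both numbers are printed and equal, so no assumption held elsewhere can create a margin between them.
- **The trial calls itself an exploratory pilot.** This lowers the consequence. It does not explain the printed power claim or the superiority wording in the Abstract and Conclusion.

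The first two points limit the size of the problem. None of the four restores an allowance.

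**Conclusion.** The point holds in a limited form. The 70% is quoted at the full recruitment number, so any participant withdrawn and discarded under the Study procedures rule takes the analysed sample below the one it is quoted for. The size depends on how many are lost. In the illustration, the granted 70% drops by about 12, 28 and 42 percentage points at 25%, 50% and 69% loss. That rests on the face-value 70% at 50 per group, equal loss in both arms, and every lost participant's data being discarded.

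A reader might take 58%, 42% or 28% as this trial's actual power. The documents do not support that, because the starting 70% does not itself reproduce for an odds ratio of 2.0 at 50 per group, and because 50 per group is twice the number of children per arm. Both are separate defects that a dropout allowance alone would not repair. That is why the figure should be recomputed rather than scaled down.

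**What to change.** In Proposed analysis, remove the unqualified 70%. Recompute power from stated inputs (endpoint definition, control rate or SD, any correlation relied on) at the expected analysable number of children per arm under an explicit attrition assumption, for example with a row each for 0%, 25%, 50% and 69%. Do not derive the new figures by scaling the 70%.

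Keep the planned enrolment. Bring the superiority wording in the Abstract and Conclusion into line with the exploratory aim in Proposed analysis, by saying that the ECBI difference will be reported as an estimate with its confidence interval.

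The cost is a short table or a few sentences and a less favourable stated power. Recruitment and procedures do not change.
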